### Statistical analyses

This clinical trial will be conducted in compliance with the protocol of the Declaration of Helsinki and GCP. Aiming at an intention-to-treat design we will include all participants who will be randomly assigned to conditions. Additional per protocol analyses (PPA) will be conducted, including only participants’ satisfying protocol treatment.

Missing data will be handled using multiple imputations (MI). MI is especially robust with respect to missing data [69]. Nevertheless, to assess systematic effects of missing data that cannot be ignored, pattern mixture analyses for multi-level longitudinal approaches [70] will be conducted. To determine whether the treatment effect is dependent on missing data, the missing-data pattern of each participant will first be coded and then included in a three-way interaction (missing-data pattern x condition x change in depression severity) in the main outcome analyses. If no significant interactions between the missing-data pattern and the treatment outcome are found, it can be concluded that it is very unlikely that missing data skewed the results.

The mean improvement scores on all continuous outcome measures will be analysed within and between groups via mixed-model analyses of variance. For all mixed-model analyses, Cohen’s *d*[71] will be calculated by standardising the differences between baseline and follow-up scores by the pooled standard deviation of baseline scores.

The clinically significant improvements between pre-treatment and post-treatment will be examined with regard to the definition of Kroenke (2002) [58]. Differences in response and remission rates will be analysed using chi-square tests. We will also calculate the number needed to be treated (NNT) to achieve response, partial remission, or remission. Time to remission will be measured in days, and the differences between groups in time to remission will be compared using a t-test for independent samples.

Analyses will be performed using an alpha level of 0.05 and one-sided tests will be used for unidirectional and two-sided tests for bidirectional hypotheses. All analyses will be conducted using SPSS 21.

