### Sample size

This study will be designed to detect a difference of *d* = 0.40 between the groups as the primary outcome. As patients expect to be treated for their depression in the subsequent inpatient psychotherapeutic treatment, we do expect a somewhat smaller effect size for our intervention than what has been found in the most recent meta-analysis of internet-based guided self-help treatments for depression [35]. With a power of 0.80 in a two-tailed test and *α* = .05, a sample of *n* = 200 participants would need to be included at baseline (calculated using GPower 3.1).

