### Primary and secondary outcomes

#### Primary outcome

The primary outcome is depressive symptom severity, as measured by the Hamilton Rating Scale for Depression (HRSD_24_) [51], with assessments conducted pre-and post-treatment. The HRSD is likely the most widely used clinician-rated scale for measuring depression. It assesses depressed mood, vegetative and cognitive symptoms of depression, and anxiety symptoms during the prior seven days. Items are rated on either a five-point or a three-point scale, and the total score is derived by summing the individual item scores. Higher scores indicate greater symptom severity. The HRSD has an interrater-reliability of 0.90 [51] and shows high internal consistency (*α* = 0.88) [52]. Furthermore, it is sensitive to change over time and treatment and corresponds well with overall clinical ratings of severity [53,54]. The cut-off points of 10, 19, 27, and 35 represent the thresholds for mild, moderate, severe, and very severe depression, respectively [52].

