#### Secondary outcomes

##### Depressive symptomatology

Observer-based ratings of depressive symptom severity will additionally be collected using the 16-item Quick Inventory of Depressive Symptomatology–Clinician-Rating (QIDS-CR_16_) [52] to achieve a more nuanced understanding of the symptom severity. The QIDS-CR_16_ is a brief clinician-report rating scale developed from the 30-item Inventory of Depressive Symptomatology [55,56]. Unlike the HRSD, the QIDS-CR_16_ evaluates only the nine depression criterion symptom domains (i.e., sad mood, concentration, self-criticism, suicidal ideation, interest/involvement, energy/fatigability, sleep disturbance, appetite/weight change, and psychomotor agitation/retardation) from the Diagnostic and Statistical Manual of Mental Disorders (Fifth Edition) [57] during the prior seven days. Each item is scored on a scale from 0 to 3 points, with higher scores indicating higher symptom severity. This measure has shown good psychometric properties, such as strong internal consistency (*α* = 0.85), concurrent validity, and sensitivity to symptom change in patients with MDD [56]. The cut-off points of 6, 11, 16, and 21 represent the thresholds for mild, moderate, severe, and very severe depression, respectively.

Self-reported depressive symptoms will be assessed with the Patient Health Questionnaire (PHQ-9) [58]. This measure has comparable sensitivity and specificity to many other depression measures, although it is significantly shorter than most other measures [59]. The internal reliability of PHQ-9 reaches values between *α* = 0.86 and 0.89. The score ranges from 0 to 27 because each of the nine items can be scored from 0 (“not at all”) to 3 (“nearly every day”). The cut-off points of 5, 10, 15, and 20 represent the thresholds for mild, moderate, moderately severe, and severe depression, respectively [58,59].

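### For HRSD, a non-significant missing-data-pattern interaction cannot support the plan's conclusion that missing data are very unlikely to have skewed the results

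*Protocol article*

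**What the plan says.** The Statistical analyses section of the Protocol article plans multiple imputation for missing data. It then adds a pattern-mixture check for missingness that cannot be ignored. Each participant's missing-data pattern is coded and "included in a three-way interaction (missing-data pattern x condition x change in depression severity) in the main outcome analyses". The reading of a null result is fixed in advance: "If no significant interactions between the missing-data pattern and the treatment outcome are found, it can be concluded that it is very unlikely", where the unlikely event is distortion by missing data. No other analysis of non-ignorable missingness is described.

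The primary outcome is HRSD, "with assessments conducted pre-and post-treatment" (Primary outcome). Table 1 agrees and marks HRSD at T0 and T3 only. PHQ-9, a secondary outcome, is marked at every time point from T0 to T10, including T1 and T2 before the post-treatment assessment.

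**The concern.** There are two problems with the rule when it is applied to HRSD.

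- **No information.** A pattern-mixture check learns from the observed course of people who later drop out. With HRSD at T0 and T3 only, someone who misses T3 has no observed course. Any change attributed to that person comes from the imputation model, and standard imputation carries the missing-at-random assumption that the check is meant to examine.
- **Inference from non-significance.** Even with the missing scores in hand, a test of effect heterogeneity between a small dropout group and the completers would have little power. Failing to reject would say little about bias.

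At stake is the statement made about the main result. If participants with missing T3 scores benefited less than the imputation model assumes, the estimated effect would be too large. The planned check would almost always be non-significant, and the report would say that missing data are unlikely to matter.

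**Working it through.** **Inputs from the article.** HRSD at T0 and T3; N = 200; d = 0.40; power 0.80; two-sided alpha 0.05; two arms. **Assumptions, not in the article.** 1:1 allocation; 5% to 40% of T3 scores missing; T0–T3 correlation 0.5; an auxiliary correlated 0.7 or 0.85 with T3 HRSD and observed for dropouts.

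**1. The plan's own figure.** n per arm = 2(1.960 + 0.842)²/0.40² = 98.1, so 99 by the normal approximation. The t-test solution is 99.08, rounded up to 100 per arm, or 200 in total, with power 0.804. The stated sample size reproduces.

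**2. Estimability.** Write the model with 8 terms: intercept, condition, time, pattern, condition × time, condition × pattern, pattern × time, and pattern × condition × time. If pattern = 1 means that T3 is missing, no observed row has both pattern = 1 and time = 1. The last two columns are therefore zero in every observed row. The design matrix has rank 6, and the interaction that the rule tests is not estimable from observed HRSD.

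**3. The test on imputed values, no effect in dropouts.** The effect is 0.40 SD in completers and zero in participants with missing T3, with equal missingness m in both arms. The true overall effect is (1 − m) × 0.40. Imputation from arm and baseline returns the completers' effect, so the expected overstatement is m × 0.40. The imputation columns give the simulated estimates (800 to 1500 trials per setting).

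| m | Truth | MI, arm and baseline | MI, auxiliary r = 0.7 | MI, auxiliary r = 0.85 | m × 0.40 |
|---|---|---|---|---|---|
| 5% | 0.38 | 0.40 | 0.39 | 0.38 | 0.02 |
| 10% | 0.36 | 0.39–0.40 | 0.39 | 0.37 | 0.04 |
| 20% | 0.32 | 0.39–0.41 | 0.37 | 0.34 | 0.08 |
| 30% | 0.28 | 0.40 | not run | not run | 0.12 |

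With arm-and-baseline imputation the interaction was never significant (for example, 0 of 1500 trials at 20% and 0 of 1500 at 30%). Across the 5% to 20% runs, with the auxiliary included, it was significant in 0% to 6% of trials.

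**4. A harsher mechanism, as a stress test.** The true effect is 0.40 SD in everyone and about 20% of T3 scores are missing. In the intervention arm a poor outcome raises the chance of being missing, in three strengths (1000 trials each).

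- Arm-and-baseline imputation: estimates 0.55, 0.63 and 0.66; no significant interaction in any trial.
- Auxiliary with r = 0.7: estimates 0.47, 0.53 and 0.56; interaction significant in 2.3%, 6.2% and 7.9% of trials, against 0.1% when there was no bias.

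**5. Power if dropouts' scores were known.** With correlation 0.5 the SD of change is √(2(1 − 0.5)) = 1. The unadjusted contrast has SE = √(2/n_dropout + 2/n_completer), with n per arm. At 20% missing, SE = √(2/20 + 2/80) = 0.354. The interaction detectable with 80% power is 2.80 × 0.354 = 0.99 SD. Power for 0.40 SD is Φ(0.40/0.354 − 1.96), plus a negligible second tail, or about 0.20.

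| Missing | SE | Power for 0.40 SD | Detectable at 80% power |
|---|---|---|---|
| 10% | 0.471 | 0.14 | 1.32 |
| 20% | 0.354 | 0.20 | 0.99 |
| 30% | 0.309 | 0.25 | 0.86 |
| 40% | 0.289 | 0.28 | 0.81 |

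Baseline adjustment at 20% missing gives SE = 0.354 × √(1 − 0.5²) = 0.306 and power of about 0.26, which is still low.

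**The case against.** The strongest defence is that this is one interpretive sentence about a sensitivity check. Multiple imputation remains the main analysis, so the primary estimate and its test are the same with or without the rule. That stands, and it limits the severity. Imputation predictors and the form of sensitivity analyses are also commonly left to a fuller document, so their absence is not held against the article. The stated inference is different: it is fixed in the text.

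A reader might infer more than the documents support in four ways.

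- *That the plan claims proof, or would clear itself whatever the truth.* The article says only that distortion is very unlikely. It does not define how patterns are coded. If they include missed PHQ-9 assessments, some patterns would have an observed HRSD change and the test could be significant. It would still say nothing about the unobserved HRSD scores.
- *That leaving the online programme removes the HRSD in one arm.* It does not by design. Blinded interviewers collect HRSD by telephone (Assessments; Blinding), and the Discussion sets the post-treatment assessment at three weeks after randomisation in both conditions, expecting participants to be at different stages of the training. Differential missingness is possible but assumed.
- *That a particular bias is to be expected.* The sizes depend on assumed missingness, effect in dropouts and imputation model. Nothing in the article excludes T1 and T2 PHQ-9 from the imputation, and a strong auxiliary reduces the bias.
- *That the check is equally empty, or has very low power, for weekly PHQ-9.* There, dropouts can have observed scores before they leave, and the method cited is meant for longitudinal data. The power figures above are for a two-time-point contrast and do not carry over.

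None of this rescues the inference for HRSD.

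**Conclusion.** The rule licenses an invalid conclusion about the primary outcome. For participants without T3 HRSD, the interaction is either not estimable or, under missing-at-random imputation, near zero by construction. Its non-significance is therefore not evidence that missing data did no harm.

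Under assumed 5% to 30% missing T3 scores and no effect in those participants, the overstatement that would go unnoticed is roughly 0.00 to 0.12 SD, against the design effect of 0.40. The lower end needs little missingness and a strong auxiliary; the upper end is 30% missing with imputation from arm and baseline. The larger shifts in step 4 need an arm-specific, outcome-driven mechanism for which the article gives no evidence. They show that the test is insensitive and are not an estimate of likely bias.

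This should be fixed. It is limited to what is concluded about missing data for HRSD and does not show that the planned primary estimate is wrong.

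**What to change.** - Delete, for HRSD, the sentence that draws a conclusion from a non-significant interaction. The pattern-mixture check can stay for weekly PHQ-9, reported with its estimate and confidence interval.
- Keep multiple imputation as the main analysis and include the T1 and T2 PHQ-9 scores, already collected, as auxiliary predictors of T3 HRSD.
- Assess non-ignorable missingness in HRSD with a delta-adjusted tipping-point analysis: shift the imputed T3 scores in steps, separately by arm, and report the shift at which the conclusion changes. Readers can then judge whether that shift is plausible.
- Reference-based imputation, with missing intervention-arm scores imputed from the TAU arm, is an optional addition.

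The cost is some extra programming and a less categorical statement about missing data. No new data are needed.

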### Inclusion and exclusion criteria

Patients will be included in this trial when they (a) are awaiting to be treated with routine mental health care at any of the three study centres, (b) are scheduled to have a waiting time of at least three weeks, (c) are 18 years of age or older, (d) meet criteria of a major depressive episode (according to DSM-V criteria), (e) are motivated to actively participate in the self-guided internet intervention to improve their depressive mood during the waiting time, (f) have access to a computer with an internet connection and a valid email address, and (g) return the signed informed consent form.

We will exclude patients with bipolar disorder or acute psychotic symptomatology (according to DSM-V criteria) or patients showing a notable suicidal risk, as assessed during the structured clinical interview.

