### Assessments

Self-report and observer-rated assessments will take place at baseline, post-intervention (three weeks after randomisation), at intake for inpatient treatment, weekly during inpatient therapy, and after completion of inpatient therapy (see Figure 1 and Table 1 for a detailed overview). Self-report data will be collected using a secure web-based assessment system (AES, 256-bit encrypted), and observer-based assessments will be conducted via the telephone by trained interviewers. Observer-rated assessments will be recorded to examine interrater reliability. In cases of disagreement, the two raters will discuss until a consensus is formed, and the rating agreed upon will be used for further analyses. If no agreement is reached after discussion, the assessment will be rated by an experienced diagnostic rater, and this rating will be used for analysis.

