##### Response remission, and time to remission

Based on the recommendation of Rush (2006), we will use a definition of response/remission that reflects a clinically significant benefit, depending on the specific setting and needs in this trial [68]. A decline in the PHQ-9-score of at least five points will be taken as a clinically significant response. Remission in this specific context will be understood as a symptom-free state, an absolute PHQ-9-score of less than ten will be defined as partial remission, and a PHQ-9-score of less than five will be defined as remission [58]. Time to remission will be defined as the number of days until the symptom-free state is achieved for the first time.

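### Response, partial remission and remission on the PHQ-9 are tested by chi-square without adjustment for the T0 PHQ-9 already collected: a valid test that gives up precision, by an amount the document does not fix (minor)

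*Protocol article*

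**What the plan says.** The Protocol article names the test in Statistical analyses: "Differences in response and remission rates will be analysed using chi-square tests". The next sentence adds "We will also calculate the number needed to be treated (NNT) to achieve response, partial remission, or remission". No covariate or adjustment is attached to either.

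The endpoints are defined under Response remission, and time to remission:
- Response is a change from baseline: "A decline in the PHQ-9-score of at least five points will be taken as a clinically significant response".
- The other two are absolute levels: "an absolute PHQ-9-score of less than ten will be defined as partial remission, and a PHQ-9-score of less than five will be defined as remission".

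Table 1 marks the PHQ-9 at T0 and at every later time point. Entry is by a diagnosis of a major depressive episode, with no PHQ-9 minimum (Inclusion and exclusion criteria). The Abstract labels the remission questions explorative. Trial objectives and purpose and the Discussion both list response and remission at the end of inpatient treatment among the questions to be examined.

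**The concern.** All three endpoints depend on where the patient started. For the absolute cut-offs, a patient just above 10 at T0 needs very little change to reach partial remission, while a patient with a high score needs a large fall. Neither the definition nor the test takes account of this. For response, T0 is part of the definition, but the test still leaves it unadjusted, and the dependence runs the other way: a higher T0 score makes a five-point fall easier.

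A 2x2 chi-square test cannot use a continuous baseline score. Two things follow. Outcome variation that T0 could explain stays in the error, which costs power. A chance difference in T0 PHQ-9 between the arms also feeds, in part, into the rates and the NNTs, and the NNTs are the figures that clinics are likely to quote. The sample size is set for the primary outcome only, so nothing in the plan protects power for these endpoints.

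**Working it through.** **Inputs from the article.** The Sample size section plans for "a difference of *d* = 0.40 between the groups as the primary outcome" and continues "With a power of 0.80 in a two-tailed test and *α* = .05", with 200 participants.

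**Reproducing the stated figure.** Normal approximation: n per arm = 2(1.960 + 0.842)² / 0.40² = 98.1, so 99 per arm, 198 in all. The t-test calculation gives 99.08, so 100 per arm, 200 in all, with power 0.804. The stated 200 is reproduced.

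**Inputs the article does not give, so assumed.** 1:1 allocation; a PHQ-9 shift equal to the d = 0.40 planned for the HRSD; baseline-to-follow-up correlation 0.2 to 0.7; the control rates shown below; two-sided tests at 0.05. (The article allows one-sided tests for unidirectional hypotheses and does not say which applies here.)

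**Power by simulation.** PHQ-9 was rounded and truncated to 0–27, with assumed baseline mean 16 and SD 5, 100 per arm, and thousands of runs per case. Pearson chi-square was compared with logistic regression on arm plus T0 PHQ-9. Control rates were about 31% for each absolute cut-off and 37 to 41% for response.

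| Correlation | Response: chi-square / adjusted | Partial remission | Remission |
|---|---|---|---|
| 0.2 | 0.443 / 0.545 | 0.602 / 0.604 | 0.603 / 0.609 |
| 0.4 | 0.562 / 0.620 | 0.606 / 0.640 | 0.599 / 0.645 |
| 0.5 | 0.634 / 0.679 | 0.601 / 0.675 | 0.598 / 0.666 |
| 0.6 | 0.707 / 0.749 | 0.601 / 0.705 | 0.594 / 0.702 |

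A second model used untruncated normal scores at correlation 0.5. For absolute cut-offs with control rates of 10, 20, 30 and 50% it gave 44 vs 49, 54 vs 61, 60 vs 67 and 61 vs 69%. For response it gave 44 vs 49, 54 vs 61, 59 vs 67 and 60 vs 68%.

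Taking all models together over correlations 0.2 to 0.7, the gain at d = 0.40 is about 0 to 18 points for the absolute cut-offs, rising with the correlation. For response it is about 3 to 13 points, falling as the correlation rises, because a change score already removes more of the baseline when the correlation is high.

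**Validity.** Under no effect, chi-square rejected in 4.7 to 4.9% of runs and the adjusted test in 4.5 to 5.0%.

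**Discharge.** If the effect has shrunk to d = 0.20 and the correlation with T0 is 0.2 to 0.3, power for absolute cut-offs (control rates 30 and 50%) is 19–22% by chi-square and 19–21% adjusted: no gain.

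**NNT under chance imbalance (correlation 0.5, d = 0.40).** One standard error of the baseline difference is 5 × √(2/100) = 0.71 PHQ-9 points.
- Partial remission: risk difference 0.461 − 0.309 = 0.152, NNT 1/0.152 = 6.6. The imbalance moves the difference by 0.0274, so the NNT becomes 1/0.179 = 5.6 or 1/0.125 = 8.0.
- Response: risk difference 0.538 − 0.380 = 0.158, NNT 6.3. A shift of 0.0288 gives about 5.3 or 7.7, and here the arm with the higher T0 score is favoured.

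**Precision.** For partial remission the standard deviation of the risk difference falls from 0.0683 to 0.0627 on standardising over baseline. The variance ratio is (0.0627/0.0683)² = 0.84, about 16% lower.

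**The case against.** The case for leaving the text alone is substantial.

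- Chi-square on two randomised proportions is valid and transparent, and the simulations confirm its type I error. A reader might infer that the unadjusted test is biased or wrong. The article does not support that: allocation is random, so a chance T0 imbalance is ordinary sampling error. It also reaches the rates only in attenuated form, by about 2.6 to 2.9 percentage points per standard error at correlation 0.5.
- The remission questions are explorative and power for them was never a design target. The PHQ-9 is also analysed as a continuous measure by mixed models, which use the T0 score.
- A reader might say that baseline is ignored throughout. For response that is inexact, because T0 enters the definition.
- A reader might quote a loss of 5 to 8 points as a property of the plan. That figure needs a correlation near 0.5, which the article does not give.
- The d = 0.40 belongs to the HRSD three weeks after randomisation. By discharge both arms have had a variable wait and usually 21 to 56 days of inpatient care, so a smaller effect and a weaker correlation are plausible. Selection on severity could also narrow the T0 spread, and nothing in the article suggests many patients would score very low at T0.

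All of this stands. It limits the size and weight of the point. It does not remove it: the covariate is already collected, adjustment kept the error rate near 5%, and in the settings examined it cost essentially no power even where it brought little.

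**Conclusion.** The concern holds as lost precision on exploratory endpoints. At 100 per arm and d = 0.40, the unadjusted test gives up about 0 to 18 power points for partial remission and remission, and about 3 to 13 for response, with about 5 to 8 points as the middle case at correlation 0.5. For remission at discharge the loss may be negligible. Every one of these figures rests on an assumed correlation, control rate and PHQ-9 effect, and on two-sided testing with equal arms. The article supports no single number. The NNT example shows a practical consequence: an ordinary chance imbalance can move an NNT of 6.6 to anywhere between about 5.6 and 8.0 at correlation 0.5. Severity: minor.

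**What to change.** In Statistical analyses, replace the chi-square sentence for the three binary endpoints with logistic regression on condition, with T0 PHQ-9 as a continuous covariate. Average the fitted probabilities over the whole sample under each condition. Report the resulting standardised risk difference with its confidence interval, and take the NNT as its reciprocal. Keep the crude rates and the chi-square test as supportive results.

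One detail needs care. Assessment of eligibility and randomisation lists allocation ahead of the initial assessment. The covariate should be a T0 score taken before the patient knows the allocation, and the text should say so.

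The cost is a sentence or two of wording and a little more programming, with no new data or patients. The small downside is that the odds ratio is conditional on baseline, so the standardised risk difference has to be reported with it.

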## Background

Major depressive disorder (MDD) is one of the most prevalent psychiatric disorders, with a lifetime prevalence that is currently estimated at about 16% [1-3] and predicted to further increase in the foreseeable future [4,5]. By 2030, depressive disorders are anticipated to be responsible for the highest disease burden in high-income countries among all diseases [6]. Suffering from MDD is accompanied by a substantial loss in quality of life, not only for patients but also for their relatives [7-9]. Furthermore, suffering from a depressive episode is associated with a high risk of relapse and recurrence [1,10] as well as a chronic course [11], increased mortality rates [12], significant disability, high medical service use, and major economic costs [13-16].

Although numerous studies provide evidence for the efficacy of available psychological and pharmacological treatments [17,18], many individuals remain untreated [19,20]. The reasons for this treatment gap are twofold. First, individuals who likely to benefit from treatment do not seek treatment because they lack knowledge on available treatment options, anticipate negative (social) consequences, live in underserved areas, fear prohibitive costs, or prefer self-help [20]. Limited availability of clinicians and difficulties in attending therapy during usual business hours are further barriers [21]. Second, those who do seek help rarely receive immediate access to treatment due to long waiting lists for both inpatient and outpatient psychotherapy [20,22]. Consequently, people with an urgent need for therapy are left alone with their burden, which poses several ethical, practical, and therapeutic problems. In addition to high levels of suffering, long waiting times might increase symptom severity and hence increase the need for more intense and longer treatments [23,24].

Another related problem is that because of factors such as limited financial resources and time, inpatient patients are often discharged from the clinic at a very early stage, leaving them with substantial residual symptoms. However, even low levels of residual symptoms are known to increase the risk for relapse and recurrence [25-28]. Recent meta-analyses show that between 40 and 60% of patients with MDD relapse after the initial response to an acute-phase treatment [27].

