#### Inpatient treatment–both groups

Inpatient treatment will generally base on Cognitive Behavioral Therapy (CBT). Patients will receive one to two session of individual therapy (50 minutes) and an average of six sessions of group therapy (90 minutes) per week. Interventions will be supplemented with sports-and physiotherapy, as well as medical treatment (including medication) when necessary. Duration of treatment usually range between 21 and 56 days.

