This trial has also several limitations: As the trial will be conducted within the context of routine mental health care, the time span between the post-treatment assessment (conducted after the web-based treatment) and the beginning of inpatient therapy depends on both the capacities of the clinic and the eagerness of the patient and therefore will vary between patients. We will assess post-treatment data in both conditions at three weeks after randomisation to ensure a comparable time frame. Hence, patients will be at varying states within the online training when the post-treatment assessment takes place. Furthermore, we chose not to include a placebo/attention control condition because the TAU condition cannot be foreknown and is expected to be quite heterogeneous. Besides it is our aim is to study the effectiveness of GET.ON Mood Enhancer-WL in addition to and compared with usual care, as is standard in pragmatic trials [72]. However, due to the lack of such an active control condition, the mechanisms responsible for any possible effects will remain unclear. Last, we will include follow-up assessments only until the end of inpatient treatment. Therefore, we cannot draw conclusions about the effects on the long-term course of symptoms.

In the long term, it would be a desirable step to increasingly implement a new procedure such as this into the daily routine of inpatient as well as outpatient therapy. It would be good practice for the therapist to know in detail what steps the patient has taken previously and to be able to continue the previous gains. This knowledge would assist both the patient and the therapist, saving time and effort, and allowing them to concentrate on further issues and to intensify the treatment process.

Future research could make use of a homogenous control group, focus on various modifications of the program to identify active ingredients, compare different interventions that are likely to be effective as pre-inpatient treatments, evaluate web-based interventions for other disorders than depression or change the setting into the field of outpatient therapy.

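### The t-test named for time to remission has no value for patients who are not remitted at discharge; a survival analysis in all randomised patients is needed

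*Protocol article*

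**What the plan says.** All references are to the protocol article.

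- **Variable** (Response remission, and time to remission): "Time to remission will be defined as the number of days until the symptom-free state is achieved for the first time". The threshold is that "a PHQ-9-score of less than five will be defined as remission". No time origin is stated, and no value is defined for a patient who never reaches the threshold.
- **Test** (Statistical analyses): "the differences between groups in time to remission will be compared using a t-test for independent samples".
- **Population** (same section): "Aiming at an intention-to-treat design we will include all participants who will be randomly assigned to conditions". Missing data are to be multiply imputed.
- **End of observation** (Discussion, limitations): "we will include follow-up assessments only until the end of inpatient treatment". On length of stay, the inpatient treatment section says: "Duration of treatment usually range between 21 and 56 days".
- **Non-remission is expected** (Background): "inpatient patients are often discharged from the clinic at a very early stage, leaving them with substantial residual symptoms".
- **Status**: the Abstract labels earlier remission an explorative question, and Trial objectives and purpose says it will be explored. The Discussion lists it as question (b), after the main hypothesis on symptom severity.

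**The concern.** A t-test compares means and needs a number for every patient. Here a patient discharged with PHQ-9 of 5 or more supplies only a lower bound, and that bound differs between patients because stays differ. Multiple imputation does not fill the gap: not remitted by discharge is an observed non-event, not a missing score.

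That leaves two ways to run the named test. Dropping non-remitters compares groups formed by an outcome of treatment, contrary to the promise to include everyone randomised. Assigning non-remitters a time makes the result depend on a rule the protocol does not contain.

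At stake is whether patients remit earlier. A remitters-only mean is truncated by discharge in both arms, so a real acceleration can be nearly invisible. If the intervention mainly adds late remitters, the mean can even move the wrong way. Censoring may also depend on treatment, because the Abstract hopes the intervention will shorten inpatient therapy.

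**Working it through.** **1. The protocol's own figure.** Sample size gives 200 participants for d = 0.40, power 0.80, two-tailed alpha .05. The exact noncentral t gives 100 per arm, power 0.804, so 200 reproduces. It covers the HRSD primary outcome only; no power, remission rate or event count is given for time to remission.

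**2. Why a remitters-only mean hides an effect.** Assume exponential times and a common window T = 70 days (3 weeks plus a 49-day stay). Among remitters the mean is T × [1/(λT) − 1/(e^(λT) − 1)].
- Control remission 30%: λT = −ln 0.70 = 0.357; mean = 70 × (2.804 − 2.333) = 32.9 days.
- Hazard ratio (HR) 2.0: λT = 0.713; mean = 70 × (1.402 − 0.961) = 30.9 days.

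Doubling the remission hazard shows as a difference of about 2 days. A simulation on a weekly grid gives 1.98.

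**3. Power under three ways of running the t-test.** From the protocol: 200 patients, weekly PHQ-9, stays of 21-56 days. Assumed: 1:1 allocation, exponential times rounded up to weeks, stays uniform and rounded down to weeks, control remission by day 38.5 (mid-stay) as shown, two-sided 0.05. Ranges cover repeated runs.

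| Control remission | HR | t-test, remitters only | t-test, last observed day | t-test, common value of 63 days | Log-rank |
|---|---|---|---|---|---|
| 25% | 1.5 | 3-4% | 15-16% | 30-33% | 32-34% |
| 35% | 1.5 | 5% | 23-25% | 40% | 40-42% |
| 50% | 1.5 | 7-8% | 36% | 51-53% | 52-55% |
| 25% | 2.0 | 4-5% | 41-45% | 74-75% | 76-77% |
| 35% | 2.0 | 7-9% | 63-66% | 87-88% | 88-89% |
| 50% | 2.0 | 17-19% | 83-86% | 95-96% | 96-97% |

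At 70% control remission and HR 2.0, the remitters-only test reaches 47-48%.

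**4. A second censoring set-up.** Censoring was fixed at day 70 or spread over days 42-77 (3 weeks plus the stay), with control remission of 20-70% by day 70. At HR 1.5 the remitters-only t-test has power 4-10% for control remission of 20-50% and 14% at 70%. At HR 2.0 it has 5-19% and 42-51%. Log-rank power over the whole 20-70% range is 25-70% at HR 1.5 and 66-99% at HR 2.0.

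As a check, the Schoenfeld formula 4(1.960 + 0.842)²/(ln HR)² gives 191 remissions for 80% power at HR 1.5 and 66 at HR 2.0. With 30% control remission and HR 2.0, expect 100 × (0.30 + 1 − 0.70²) = 81 remissions, power 0.877; the simulated log-rank power is 0.81-0.88.

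**5. A different effect model.** If remitters' times shift by d = 0.40, a remitters-only t-test has power 0.23, 0.33, 0.51 and 0.65 with 20, 30, 50 and 70 remitters per arm.

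**6. Direction.** Take a fixed 49-day follow-up. In control, 30% remit evenly over weeks 1-7 (mean 28 days). The intervention arm has the same 30% plus 20% remitting in weeks 5-7 (mean 42 days). Its mean among remitters is (30 × 28 + 20 × 42)/50 = 33.6 days, which is 5.6 days slower although more patients remit. This is significant in the wrong direction in about 41-44% of simulated trials. With the extra remitters spread evenly the figure is about 3%. With them in weeks 1-3, the test is significant in the right direction in about 43-44%.

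**The case against.** The strongest reply is that the question is exploratory. The primary outcome is HRSD and the sample size rests on it. Remission rates are compared separately by chi-square with a number needed to treat, so a gain in the number of remitters is not lost. This stands and limits severity. It does not answer whether remission comes earlier.

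A reader might infer that the analysis will be confined to remitters. The protocol does not say so; it says that all randomised participants are included. What it supports is narrower: the handling of non-remitters is undefined, and the named test cannot proceed without a rule.

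A reader might also infer that the test has almost no power. That holds only for a remitters-only analysis at low to moderate remission under proportional hazards. It fails at 70% remission with HR 2.0, under a d = 0.40 shift, or if non-remitters receive a common late value. The log-rank test is itself underpowered at HR 1.5, so the t-test is not the only cause. Statistical analyses also allows one-sided tests for unidirectional hypotheses, which would raise the power figures.

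The wrong-direction result needs the extra remissions to fall late. It shows a possible bias, not an expected one.

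Finally, Table 1 has five weekly inpatient columns, from which one might infer that monitoring stops before a long stay ends. The text under Study design and Assessments says weekly during inpatient therapy, so the columns may be schematic. No point is made of this.

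**Conclusion.** The point holds as a wrongly chosen method that the protocol states, not as a detail left to an analysis plan. The t-test does not fit a right-censored time. Running it means either selecting on remission or inventing a rule for non-remitters.

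The size of the loss depends on that rule and on a remission rate the documents do not give. It runs from severe for a remitters-only test (about 3-8% power at HR 1.5 and 4-19% at HR 2.0, for control remission of 25-50%) to negligible with a common late value. These figures assume 100 per arm, proportional hazards, exponential times and two-sided 0.05. They do not model the variable wait between the post-treatment assessment and admission.

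Severity is moderate: an exploratory question is affected and the primary conclusion is not.

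**What to change.** Replace the t-test sentence with wording to this effect: time to first PHQ-9 below 5 will be analysed in all randomised patients, with those not remitted censored at their last PHQ-9. Arms will be compared by Kaplan-Meier curves, a log-rank test, and a Cox or discrete-time (weekly) hazard ratio with 95% confidence interval. The discrete-time form suits the weekly assessments.

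State the time origin. Randomisation keeps the intention-to-treat comparison. Table 1 has no PHQ-9 between the post-treatment assessment (T3) and admission (T4), so a remission in that gap is first seen at admission. Time from admission matches the question in Trial objectives and purpose and should be reported as a supporting analysis, with a rule for patients already below 5 at admission.

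Treat discharge without remission as a competing event in a sensitivity analysis, since discharge may depend on both symptoms and arm.

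The cost is a change of wording. Kaplan-Meier, log-rank and Cox procedures are available in SPSS, the named software, and no extra patients or assessments are needed. The change should be made before outcome data are seen.
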